#### Economic evaluation

We will adopt a decision analytic approach, whereby we will identify the incremental cost savings from both a health care sector and a societal perspective of the active strategy of implementation [55]. The model will consider two hypothetical cohorts of patients, a "usual practice" cohort, and a cohort where practice is as dictated through the active dissemination of the decision rule. Results will be generated through probabilistic analysis, as this is superior to simple deterministic analysis [56,57]. The principal resources in this analysis will be the costs of radiography and the associated patient time costs. In addition, the costs of settlement of litigation, the incremental costs of follow-up treatment due to missed fractures, and the costs of neurological deficits will be included. The design of the decision analytic model, sources of data, and analysis of uncertainty are provided in a supplemental file [58-64] [see Additional file 1].

### Sample size

#### Required patients

Refer to the supplemental file for more details on the sample size calculation [45,65-67] [see Additional file 2]. The study is based on a complex, stratified, matched-pair cluster design, such as a stratification factor type of hospital (teaching vs. community), a matched-pair (hospitals matched according to baseline cervical spine radiography), and cluster randomization (unit of randomization is the hospital and unit of analysis is the patient) [45,68]. Let k be the number of pairs needed to achieve power100(1-β)% for detecting a difference Δ in the cervical spine radiography event rates at the two-sided 100(1-α)% significance level. From the phase II study, the cervical spine radiography event rates for non-transfer patients at the participating sites ranged from 63.3% to 85.9%, with an average of 76% and an annual accrual per hospital of approximately 400 patients. We estimate that the between-cluster variance component is 0.00636, based on Gail et al (1992) for the COMMIT trial (i.e. *Var*(*d*_*j*_) = 0.0066125) [66]. It is expected that the event rate in the control group will not change. Based on a consensus of the participating site investigators, we believe that for the intervention group, a 15% relative decrease (or an absolute decrease of 11.4% from the baseline rate of 76%) in the event rate would be considered a minimal clinically important change (i.e. Δ = 0.114). Then for a significance level of 0.05 and power of 80%, *k *=(1.96+0.84)^2^(0.0066125)/.114^2 ^= 3.9891 and the number of matched-pairs required is (7/5)(3.9891) = 5.5847 where 7/5 adjusts for the small number of degrees of freedom [65]. Thus, six matched-pair clusters will be required with 400 patients per hospital for each of the ''before'' and ''after'' periods in the primary analysis. Because the exact benefits of stratifying by teaching and community hospitals in this matched-pair design are difficult to quantify, a conservative approach is adopted and the six matched-pair clusters will be selected [67]. Furthermore, we estimate that the sample size for the ''decay'' period will be the same as for the ''after'' period, and that this will allow sufficient power in the secondary analysis to identify complete decay of effect from the ''after'' to the ''decay'' period. In addition, this will provide a sufficient sample to calculate a precise estimate of the decay rate.

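### The two variances printed in the sample size calculation do not agree at 400 patients per hospital; depending on which is the input, six pairs give about 74% or 78% power

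*Protocol article*

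**What the plan says.** All the relevant figures are in the protocol article under Sample size, Required patients.

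- Variance: "We estimate that the between-cluster variance component is 0.00636". This is attributed to a cited community trial and followed by an 'i.e.' that gives Var(d_j) as 0.0066125.
- Error rates: "for a significance level of 0.05 and power of 80" per cent, with the test "at the two-sided 100(1-α)% significance level".
- Effect: "an absolute decrease of 11.4% from the baseline rate of 76" per cent, so 64.6% at intervention sites. For control sites, "It is expected that the event rate in the control group will not change".
- Result: k = 3.9891, "and the number of matched-pairs required is (7/5)(3.9891) = 5.5847", hence "six matched-pair clusters will be required with 400 patients per hospital" in each of the two periods of the primary analysis.

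The Data analysis section specifies a paired t-test on 5 degrees of freedom. The article refers to Additional file 2 for more detail on the calculation; that file is not at hand.

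**The concern.** In a matched-pair cluster design, the variance of a pair difference is a between-cluster part plus the binomial sampling error of the two hospital rates. If 0.00636 is the first part and 0.0066125 the total, only 0.0002525 remains for sampling error. That is too little for 400 patients per hospital at rates near 70%.

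The margin is thin. The formula gives 5.58 pairs, rounded up to six. A sampling term of the proper size, added to 0.00636, takes the result past six. The stated 80% power for an 11.4-point difference then depends on which printed variance is the real input.

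**Working it through.** **Inputs**, all from the sample size section: difference 0.114; rates p1 = 0.76 and p2 = 0.646; m = 400 per hospital; component 0.00636; Var(d_j) 0.0066125; multipliers 1.96 and 0.84; small-sample factor 7/5; six pairs.

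**1. The plan's figure reproduces.** k = (1.96 + 0.84)² × 0.0066125 / 0.114² = 7.84 × 0.0066125 / 0.012996 = 3.9891. Times 7/5 this is 5.5847, so six pairs.

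**2. Room left for sampling error.** 0.0066125 − 0.00636 = 0.0002525 (0.0002475 to 0.0002575, allowing for rounding of 0.00636).

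**3. Sampling error of a two-hospital difference.** p1q1/m + p2q2/m = 0.76 × 0.24/400 + 0.646 × 0.354/400 = 0.000456 + 0.000572 = 0.001028. The gap in step 2 is 24.6% of this, as if there were about 1,600 patients per hospital. Setting both rates to 76% gives 0.000912, and the gap is 27.7% of that.

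**4. A possible origin.** 0.114 × (1 − 0.114)/400 = 0.0002525. The gap equals what results from entering the difference of 0.114 as if it were one proportion. The article does not show this step, so it is an inference.

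**5. If 0.00636 is the input.** Var(d_j) = 0.00636 + 0.001028 = 0.007388. Then k = 7.84 × 0.007388 / 0.012996 = 4.457, and × 7/5 = 6.24, so seven pairs.

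**6. If 0.0066125 is the input and already contains sampling error.** The component is 0.0066125 − 0.001028 = 0.0056. The pair count stays at 5.58.

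**7. Power for 11.4 points with six pairs.** The t-test figures use the noncentral t with 5 df and noncentrality 0.114/√(Var/6), two-sided 0.05. The approximation is the plan's own: normal, with 6 × 5/7 effective pairs.

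| Var(d_j) | Noncentrality | Power, 5-df t-test | Power, plan's approximation | Difference detectable with 80% power (t-test) |
|---|---|---|---|---|
| 0.0066125 | 3.43 | 78.2% | 82.7% | 11.7 points |
| 0.007388 | 3.25 | 73.8% | 78.4% | 12.3 points |

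Simulation of the t-test gives 78.3% and 73.8%. With seven pairs and the larger variance, t-test power is 83.1%.

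**The case against.** The strongest reply is that only 0.0066125 enters the formula. That figure equals 2 × (0.23/4)² exactly, and the stated site rates run from 63.3% to 85.9%, a range of 0.226, which rounds to 0.23. A variance built from the spread of observed site rates already contains sampling error. Adding 0.00103 would count it twice, six pairs would stand, and 0.00636 would be a misstated by-product. The article does not give this derivation and ties the estimate to a cited trial, so it cannot be confirmed. It cannot be ruled out either, and Additional file 2 may settle it. This objection stands against any one-way correction. It does not remove the inconsistency.

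A reader might infer more than the text supports in three ways.

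- *That power is 74% outright.* This requires 0.00636 to be the input. Even then, about 2 of the 6 points below 80% come from using the exact 5-df t-test, which gives 78.2% at the stated variance. The variance itself costs 4.4 points.
- *That 0.00636 is per hospital and must be doubled.* Nothing in the text says so. The quantity in the formula is the variance of a pair difference.
- *That power is lower still because the analysis uses before-to-after change.* Change scores add before-period sampling error but also remove stable hospital differences. The article gives no between-period correlation, so the net effect cannot be computed.

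**Conclusion.** The inconsistency is established: at 400 patients per hospital, 0.00636 and 0.0066125 cannot both be right, because their gap is about a quarter of the binomial error of a two-hospital difference. Which one is wrong is not established.

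- On the plain wording, where 0.00636 is what was estimated, the plan's formula needs 6.24 pairs. Six pairs then give about 74% power by the planned test, or about 78% by the plan's approximation.
- If 0.0066125 is the input and includes sampling error, only the component is misprinted. Six pairs stand by the plan's formula, with about 78% power by the planned test.

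Both branches take the chosen variance as per pair and count sampling error from one period only. The consequence is modest: a design figure and the power statement need correcting, and the design itself need not change.

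**What to change.** In the sample size section:

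1. State which variance is the input, where it comes from, and that it is per pair.
2. Use p1q1/m + p2q2/m for the sampling term, and correct the other figure to match. That means Var(d_j) of about 0.0074 if 0.00636 is the input, or a component of about 0.0056 if 0.0066125 is.
3. Restate power for 11.4 points with six pairs under the 5-df t-test as about 74% or 78% accordingly, or give the difference detectable with 80% power as 12.3 or 11.7 points.

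The cost is restated figures only, with a slightly less favourable power statement. The number of sites and patients does not change.

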#### Feasibility and timing

Hence, we will require 4,800 eligible patients at the 12 sites for each of the three study periods, for a total of 14,400 patients. We plan three consecutive 12-month periods representing, respectively, the "before," "after," and "decay" periods. Based upon our knowledge of seven sites from phase II, and extrapolating from census information of five new sites, we expect no difficulty in achieving our sample size goals. Because all eligible patients are enrolled by default, and because no consent is required, we will not lose patients to physician non-compliance nor to patient refusal.

### Methodological issues

Why a matched-pair design? The matched-pair design is frequently used in community intervention studies and offers several advantages for studies like ours, in which the unit of allocation is the hospital rather than the patient. Matching on baseline data, such as radiography rates from the "before" period, helps prevent imbalance between the control and intervention groups. This design helps preserve power of analysis when relatively few (12) clusters are being studied.

Why three study periods? The "before" period will provide the baseline radiography rates, which will be the basis for the matching and the baseline for measuring change. The "after" period will measure the time to onset of the effect of the intervention, as well as the maximum effect. The "decay" period will allow us to evaluate the sustainability of the effect of implementation, such as whether our simple and inexpensive implementation strategy can be expected to have a long-term effect.

Will incorporation of phase II sites in phase III lead to contamination? Seven of the 12 sites participated in phase II, which will end at least six months prior to the onset of phase III. We believe there will be little or no carry-over effect on physician behavior in phase III because physicians did not apply the rule in phase II, but continued to order radiography according to their judgment. If anything, physicians ordered radiography at a higher rate (71.7%) during phase II than during the phase 0 baseline (58.0%).

## Discussion

### Relevance

Blunt trauma is a very common condition that is associated with excessive and variable use of radiography, and with prolonged periods of patient immobilization in the ED. The Canadian C-Spine Rule has been derived and validated in more than 16,000 patients, and would appear to have the potential to lead to important reductions in the use of radiography, health care savings, and diminished waiting times in our crowded EDs. However, many decision rules and guidelines have no impact on health care because of inadequate dissemination strategies. What we hope to demonstrate in the proposed phase III implementation study would affect an actual change in clinical behavior. We propose to evaluate the effectiveness of implementing the Canadian C-Spine Rule, and whether such implementation can be achieved with simple and inexpensive measures. We believe that the Canadian C-Spine Rule has the potential to significantly reduce health care costs and improve the efficiency of patient flow in busy Canadian EDs.
